## Specific Procedures

### Minimizing Inter-Rater Measurement Bias

The medical doctor who will administer the stimulation will always be the same; however, assessors will change between pre and post-measurements. To minimize biases deriving from inter-rater measurement errors, the following interventions will be performed before the start of the trial:

Collegial assessments to standardize administration modalities and scoring procedures.Development of an “assessment manual” containing all information for administering and scoring procedures.

### Assignment of Interventions and Data Management

#### Allocation

Participants will be allocated randomly in the active rTMS group or the SHAM placebo group. A blocked randomization list (2:2 per group) will be generated using the online software QuickCalcs (www.graphpad.com). Only the PI and the physician administering i-rTMS will have access to the randomization list.

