## Methods and Analysis

### Study Design

The SMaRT TraCE trial (“Stimolazione Magnetica Ripetitiva Transcranica nel Trauma Cranio-Encefalico”; in English: repetitive transcranial magnetic stimulation in traumatic brain injury) is a single-blinded randomized controlled trial (RCT) with pre-test, post-test, and 12 weeks follow-up assessments. The design provides two parallel groups of patients with LHSN symptoms after TBI (i-rTMS + VST and SHAM + VST) with a 2:2 randomized allocation ratio in a superiority trial design. Figure 1 shows the study flowchart.

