### Participants

Patients with LHSN due to TBI will be recruited in the Neurorehabilitation Unit of the IRCCS Istituto delle Scienze Neurologiche di Bologna. Subjects will be recruited accordingly to the following eligibility criteria:

Inclusion Criteria:

Diagnosis of TBI;Diagnosis of LHSN with specific assessment tests [asymmetry score in the Bells test > 3, (22)];Intra-hospital rehabilitation setting (ordinary hospitalization or DH);Age between 18 and 80 years;Time after injury between 3 weeks and 1 year;Level of cognitive functioning (LCF ≥ 5);Adequate language comprehension to give informed consent. Language comprehension will be considered satisfactory if equal or superior to 75% in ordinary conversation, in the presence of an aphasic disturbance or deafness. Use of eventual hearing aids is allowed. In case of doubts, a simple or language comprehension test (token test) will be administered.Presence of inter-hemispheric asymmetries in the EEG activity evidenced by qualitative evaluation;

Exclusion Criteria:

Medical instability at enrollment, defined as the acute onset of an unexplained derangement of vital parameters (i.e., temperature, blood pressure, pulse rate, respiratory rate, oxygen saturation, level of responsiveness) outside the normal range (for example, fever, acute internist conditions, etc.) and/or the onset of any new medical condition requiring unexpected additional diagnostic procedures and treatments (for example, severe pain, reduction of urinary output, etc.);Presence of epileptogenic alterations to the EEG and/or previous epileptic seizures;Presence of intracranial implants of a metallic material;Presence of devices that could be altered by i-rTMS, such as pacemakers, ventriculoperitoneal shunt, baclofen pump;Decompressive craniectomy;Drugs conditioning the state of consciousness-vigilance such as benzodiazepines;Cortical blindness and/or visual agnosia;Concomitant psychiatric disorders and/or history of substance abuse;Post-traumatic agitation;Post-traumatic complications (i.e., hydrocephalus).

The principal investigator (PI) or a delegate will check the eligibility criteria before enrollment. After verifying the eligibility criteria, the PI will provide eligible patients and their caregivers with all the information and details relative to the study in simple language.

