#### Data Collection and Management

All data will be anonymized, and a specific alpha-numeric code will be attributed to each subject after enrolment. An electronic study database will be configured with all patient details, including the randomization group.

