### Oversight and Monitoring

A designated external committee will perform data monitoring, database, and statistical analysis management. Statistical analyses over the complete dataset will be performed at the end of data collection. However, interim analyses approved by the local ethical committee may be performed. The PI will coordinate clinical trial's organizational, ethical, and scientific aspects. Only the PI can declare the end of the enrolment.

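### The PI recruits patients and also has access to the randomisation list, so allocation is not concealed from recruitment

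*Protocol article*

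**What the plan says.** All of the relevant text is in the protocol article.

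- **Allocation:** "A blocked randomization list (2:2 per group) will be generated using the online software QuickCalcs". The next sentence settles access: "Only the PI and the physician administering i-rTMS will have access to the randomization list".
- **Participants:** "The principal investigator (PI) or a delegate will check the eligibility criteria before enrollment". Then: "After verifying the eligibility criteria, the PI will provide eligible patients and their caregivers with all the information". Some entry criteria need judgement. EEG asymmetry is rated qualitatively, language comprehension is judged against 75% in ordinary conversation, and medical instability is partly a matter of interpretation.
- **Oversight and Monitoring:** "Only the PI can declare the end of the enrolment".
- **Blinding:** assessors and the therapists giving the visual scanning treatment do not know the group, and T0 takes place before randomisation.
- **Statistical Analysis:** ANCOVA with the T0 value as covariate, with further adjustment for age, gender, education and, if it proves heterogeneous, lesion location.

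**The concern.** Randomisation protects a comparison only if those who decide on entry cannot know the coming assignment. Here one role assesses patients, talks to them and their caregivers, decides when recruitment stops, and may read the list. Knowing the next arm can influence whether a borderline patient is accepted, or when. The entry window of 3 weeks to 1 year after injury makes a delay easy. This need not be deliberate. Bias that enters this way is hard to detect and cannot be fully repaired in the analysis. In a single-centre trial of 28 patients, a few steered entries could matter.

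**Working it through.** The plan gives no figure on this point, so there is none to reproduce. The check is mainly a comparison of sections.

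**1. Who can know the next assignment, and who influences entry?**

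| Role | Access to list | Judges eligibility | Informs patients | Ends enrolment |
|---|---|---|---|---|
| PI | yes | yes, or a delegate | yes | yes, alone |
| Delegate | none stated | possibly | not stated | no |
| Stimulating physician | yes | not stated | not stated | no |

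The PI has both access and influence. Up to 28 of 28 assignments can be known to that person in advance, whatever the block size.

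**2. Do the stated safeguards close the gap?**

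- *Blinded assessors and therapists.* This guards against bias in measurement and in delivery of the training. It does not bear on who is entered.
- *T0 before randomisation.* This protects the baseline measurement. However, eligibility is checked before T0, as the caption of Figure 1 also shows, and a list can be read before either step. The order of events hides nothing from someone who has the list.
- *ANCOVA.* This removes the part of an imbalance that is carried by T0 and the other recorded covariates. A clinician's unrecorded impression of a patient's outlook is not among them.

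**3. Could a fuller protocol resolve it?** The article does not merely omit a concealment method; it states that the PI has access. An envelope procedure described elsewhere would not conceal the sequence from a person who is allowed to read the list.

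**4. Illustration of size (assumed gaps, not derived from the plan).** Let d be a prognostic difference between the arms, in SD units, that remains after adjustment, with no true treatment effect. For a two-sided 5% t-test with n = 14 per group, the degrees of freedom are 2 × 14 − 2 = 26, the critical value is 2.056, and the noncentrality is d × √(n/2) = d × √7 = 2.646 d.

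- d = 0: rejection probability 5.0%.
- d = 0.25: noncentrality 0.661, rejection probability 9.8%.
- d = 0.5: noncentrality 1.323, rejection probability 24.7%.

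With 12 per group, the number the plan expects after losses (24 in total), the last two become 9.0% and 21.6%. Nothing in the article shows that a gap of either size would arise.

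**The case against.** **A delegate may screen.** The delegate is given no access to the list, so some patients could be judged by someone who does not know the next arm. This stands as a limit on how often the problem arises. It does not remove it: nothing requires a delegate, the PI still informs patients, and only the PI ends enrolment.

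**Access is not use.** The article does not say when the list is consulted, or that anyone would act on it. That is right. A reader might infer that every assignment is known before enrolment; the text supports only that each can be known.

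**The guessing argument.** A reader might infer fixed blocks of four and conclude that the sequence is predictable. The arithmetic is correct: in a block of two and two, the chances of guessing positions one to four correctly are 1/2, 2/3, 2/3 and 1, which average 70.8%, and one third of assignments are certain. But the argument does not apply here. Both people named in the Allocation section have the list and need not guess, and the article gives the stimulating physician no part in recruitment. Block size four is itself an inference from 2:2. It fits 28 = 7 × 4, but the Study Design section uses the same expression for the allocation ratio ("with a 2:2 randomized allocation ratio in a superiority trial design"), and nothing says that the size is fixed.

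**The database.** The Data Collection and Management section says: "An electronic study database will be configured with all patient details, including the randomization group". A reader might count this as a further concealment failure. Recording past assignments does not reveal future ones. At most it concerns blinding, and the article does not say who can open the database.

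**Adjustment.** The ANCOVA would absorb part of any imbalance. This stands, and it is why the illustration above assumes a gap that remains after adjustment.

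**Conclusion.** The point holds in this form: as written, allocation is not concealed from the PI, who takes part in deciding who enters and when, so selection bias is possible. This rests on the article's own statements and does not depend on block size, on the database or on anyone's intentions. The documents do not show that bias will occur, nor how large it would be; the rise in type I error to about 10% to 25% is conditional on the assumed residual gaps. It should nevertheless be corrected, because the weakness can affect every enrolment for which the PI screens or informs the patient, it cannot be reliably undone once patients are in, and it is cheap to remove.

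**What to change.** 1. Remove the PI's access to the randomisation list, and state that no delegate who screens or informs patients has it.
2. Have the list generated and held by staff outside screening, consent, assessment and analysis. The external committee named under Oversight and Monitoring is not the right holder, because it also manages the database and the statistical analysis.
3. Replace the stimulating physician's access to the whole list with release of one assignment at a time, after eligibility, consent and T0 are complete. Sequentially numbered, opaque, sealed envelopes are enough.
4. Do not disclose the block size to recruiters, and preferably vary it.
5. For patients already enrolled, report how allocation was handled and who had seen the list.

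The cost is a short change of wording, a set of envelopes and a small amount of time from someone outside the trial team. Varying the block size gives slightly looser balance between the arms. No treatment, endpoint, analysis or sample size changes.

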#### Blinding

To ensure a double-blind assessment in all phases (T0 pre-treatment, T1 post-treatment, T2 follow-up), assessors will not be aware of the patient's randomization group. Moreover, pre-treatment assessments (T0) will be performed before randomization. Also, the visual scanning protocol will be administered by therapists unaware of the patient's allocation. Patients themselves will be instructed not to reveal any information about the brain stimulation treatment received.

#### Data Collection and Management

All data will be anonymized, and a specific alpha-numeric code will be attributed to each subject after enrolment. An electronic study database will be configured with all patient details, including the randomization group.

### Safety Assessment

Recently, guidelines for stimulation protocols were defined (39). Therapeutic interventions in clinical context should have the following properties:

The application should be easy to implement without neuroimaging and neuronavigation systems to localize the target area. Many studies, as an alternative to neuronavigation, adopt the international 10/20 localization system.The total application time of the daily rehabilitation paradigm should not exceed ten sessions during 2 weeks. Protocols that provide daily applications for more than 2 weeks are difficult to implement in rehabilitation centers and may not be tolerated by patients.

rTMS, when administered according to the international guidelines, is a safe technique.

The stimulation paradigm (9, 13, 14) reaches the guidelines mentioned above for brain stimulation protocols (39). Moreover, we followed a TMS methodological checklist (40) to report methodological details about the stimulation protocol and thus improve the quality of data collection and replicability of the study. However, adverse events are reported in the literature, as follows:

Local annoyance in the stimulated area (frequent): this effect rarely requires the suspension of rTMS.Headaches (quite frequent but usually mild). We will administer analgesics (e.g., paracetamol) in case of annoying headaches.Temporary loss of hearing (rare) for the duration of the stimulation session.Epileptic (fairly rare) crises, which occur in predisposed individuals. To minimize this risk, subjects who have suffered from seizures during the acute phase or have a diagnosis of epilepsy will be excluded from the trial (exclusion criterion).

Any adverse events during treatment will be recorded in a specific Case Report Form (CRF) and reported at the end of the study. Also, the physician who will administer i-rTMS will manage any adverse events occurring during the administration. Should the treatment be suspended, the reason will be reported. Data will be analyzed accordingly to the “intention to treat” principle and included in the study's final report.

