### Intervention

Intervention is based on previous studies (4, 9, 10) and on an RCT protocol for LHSN after stroke (13). In particular, seven sessions of i-rTMS will be administered over 15 days (9). In detail, the parameters used in each session will be:

The stimulation coil will be positioned tangentially over P5 accordingly to the international EEG 10/20 system, which corresponds to the target non-lesioned left posterior parietal cortex (4);90% of the motor threshold;Frequency: 1 Hz;Each session consisted of one train of 900 pulses, which resulted in a whole stimulation period of 15 min.

The stimulation site was chosen based on previous studies. In those studies, TMS over P5/P6 (9, 23) or P3/P4 (24, 25) was shown to reduce contralesional neglect related symptoms in patients with a unilateral brain lesion.

Each i-rTMS session will last 15 min and be administered every other day (e.g., Monday-Wednesday-Friday, Monday-Wednesday-Friday, Monday).

VST is a conventional cognitive protocol based on the administration of a structured series of tasks aiming at improving spatial exploration abilities (26). It provides various visual scanning tasks to increase the patient's awareness of the LHSN clinical manifestations and teach strategies to improve spatial exploration abilities (10). VST will be administered following the i-rTMS. In particular, three different training tasks will be used:

Visuospatial training;Reading and copying training;Copying of line drawings on a dot matrix.

All training tasks include three increasing levels of difficulty, thus giving nine possible task-difficulty combinations. Each level of difficulty will be practiced until the subject will reach a level of accuracy of 75%.

The training will be carried out in 50 min sessions for 5 days a week within 15 days (10) for 11 sessions. When the i-rTMS is also carried out, the visual scanning protocol administration will immediately follow the brain stimulation.

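### Adverse event recording is stated for the 15-day treatment period, although patients are followed to 12 weeks

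*Protocol article*

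**What the plan says.** The article's one rule on recording harms is in Safety Assessment: "Any adverse events during treatment will be recorded in a specific Case Report Form (CRF) and reported at the end of the study". Two further sentences in that paragraph concern handling and suspension: "the physician who will administer i-rTMS will manage any adverse events occurring during the administration" and "Should the treatment be suspended, the reason will be reported". Neither sets a recording period after treatment.

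The Intervention section gives the length of treatment: seven stimulation sessions on alternate weekdays and eleven visual scanning sessions, all within 15 days. Study Design describes a trial with "pre-test, post-test, and 12 weeks follow-up assessments". It does not say whether the 12 weeks are counted from the start or the end of treatment.

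Safety Assessment lists four known effects of stimulation: local discomfort, headache, temporary hearing loss and seizures. Hearing loss is tied to the stimulation session; seizures are given no time limit.

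**The concern.** The article does more than leave the recording window unmentioned. It states one, and that window is shorter than the period over which the trial observes its patients.

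The mismatch matters because benefit and harm are then followed over different periods. The third specific aim in the Introduction is a lasting reduction of neglect in daily life, and the Discussion expects the neurophysiological effect to persist at follow-up. The trial therefore assumes that stimulation may act beyond the last session and measures the benefit at T2, while harms have a stated record for the treatment period alone. The Conclusions propose use in ordinary practice if efficacy is shown, so readers will want a harms comparison to set beside the benefit.

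The patients are between 3 weeks and 1 year from a brain injury, so some events will occur regardless of arm. The sham group is what separates these from effects of stimulation. If recording stops at the end of treatment, that comparison stops with it.

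**Working it through.** The plan gives no figure on this point to reproduce. The check compares the stated recording window with the observation period.

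**Inputs**
- Treatment period: 15 days (Intervention).
- Follow-up: 12 weeks = 12 × 7 = 84 days (Study Design).
- Starting point of the 12 weeks: not stated, so both readings are shown.
- Assumption: the recording window is the whole 15-day treatment period.

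**Share of observation time inside and outside the stated window**

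| Reading | Total days | Inside | Outside |
|---|---|---|---|
| 12 weeks from start of treatment | 84 | 15/84 = 17.9% | 84 − 15 = 69 days; 69/84 = 82.1% |
| 12 weeks from end of treatment | 15 + 84 = 99 | 15/99 = 15.2% | 99 − 15 = 84 days; 84/99 = 84.8% |

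**Where the window ends relative to the last session.** The example schedule in Intervention is Monday, Wednesday and Friday in two successive weeks, then a final Monday. Counting the first Monday as day 1, the final Monday is day 15. The last stimulation therefore falls on the last day of the treatment period, and any event from the next day on is outside the stated window.

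**Whether another section closes the gap.** The Outcomes section lists neurophysiological, clinical and motor measures and no harms. Statistical Analysis mentions recording medications and relevant medical conditions on case report forms, but as additional clinical and demographic information, not as adverse events to T2. Oversight and Monitoring assigns data monitoring to an external committee without setting a recording window. No section extends the rule.

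**The case against.** The strongest reply is that the sentence says what will be recorded during treatment and does not say that later events will be ignored. This is a condensed article. The full protocol and the case report form are not shown, and detailed safety procedures are commonly left to them. That stands to this extent: one cannot conclude that the trial will in fact fail to capture follow-up events. It does not remove the point, because the article itself states a window and that window is too short for the design.

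A second reply is that most of the listed effects are acute, and that patients with previous seizures or epileptogenic EEG changes are excluded. This also stands in part. The 82% to 85% is a share of time, not of expected harms, and the documents give no basis for a number of missed events. Nor is safety a primary or secondary endpoint. But the exclusions reduce the seizure risk without removing it, and the article sets no time limit on that risk.

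Three stronger readings are tempting, and the documents do not support them:

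- A reader might infer that the external committee sees no events while patients are being treated. The article says "A designated external committee will perform data monitoring, database, and statistical analysis management", and nothing withholds case report form data from it. Reporting at the end of the study can simply mean the final report, so the two sections do not contradict each other.
- A reader might infer that an unmasked physician records the events and so could record them differently by arm. That physician does have access to allocation ("Only the PI and the physician administering i-rTMS will have access to the randomization list"), but the text has the physician manage events during stimulation. It does not say who records them.
- A reader might point to the weak upper bound that zero events in 14 active patients would give. That bound follows from the group size under any recording window and does not measure this defect.

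Finally, having masked assessors ask about harms could unmask them. The Blinding section relies on patients not discussing their stimulation with assessors, so the remedy needs a safeguard.

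**Conclusion.** The point holds in a limited form. The article fixes adverse event recording to the treatment period and does not extend it to T2. Between 69 of 84 and 84 of 99 days of each patient's observation, or about 82% to 85%, have no stated recording of harms. Followed as written, a seizure or other event between the last session and T2 would enter neither arm's record.

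This rests on reading the window as the full 15 days; if it meant the stimulation sessions alone, the gap would be larger. It also rests on the article as the only document at hand. If the full protocol already records events to T2, correcting the sentence is all that is needed.

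The effect is on the completeness of the harms comparison between arms. The primary efficacy result does not depend on it.

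**What to change.** Amend the Safety Assessment sentence so that adverse events are recorded in both arms from the first stimulation session to T2. In addition:

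- Use the same fixed checklist in both arms, with seizures as a named item, at the existing T1 and T2 visits.
- Complete the checklist after the outcomes at that visit have been scored, so that answers cannot unmask the assessor before the Behavioral Inattention Test and the Catherine Bergego Scale are rated.
- Tabulate events by arm, separately for the treatment and follow-up periods.

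The cost is about one extra case report form page at visits that already take place. Some events unrelated to stimulation will be recorded, and the sham arm and the split by period help to interpret these. A small masking risk remains, for example if an assessor who heard the T1 answers also scores T2. The order of assessment limits this risk within each visit.
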